## Abstract

Cardiorespiratory function influences exercise capacity and is an important determinant of high-altitude adaptation. Some studies have investigated the characteristics of changes in cardiorespiratory fitness during high-altitude acclimatization. However, studies on changes in cardiorespiratory fitness during high-altitude de-acclimatization are still lacking and have not yet been elucidated. Furthermore, few drugs have been studied to improve cardiorespiratory function during both processes. The Shigatse CARdiorespiratory Fitness (SCARF) study is a single-center, randomized, double-blind, placebo-control clinical trial to explore the effects of ubiquinol on cardiorespiratory fitness during high-altitude acclimatization and de-acclimatization in healthy adults. Participants will be randomly assigned 1:1 to ubiquinol 200 mg daily or a placebo for 14 days before departure until the end of data collection after return in 7 days. Cardiorespiratory fitness is the primary outcome, while acute mountain sickness and high-altitude de-acclimatization symptoms are secondary endpoints. In addition, laboratory measurements, including routine blood tests and serological measurements, will be performed. To the best of our knowledge, the SCARF study will be the first to reveal the changes in the cardiorespiratory fitness characteristics during high-altitude acclimatization and de-acclimatization. Furthermore, the results of this study will contribute to exploring whether ubiquinol supplementation could be beneficial for endurance exercise capacity at different altitudes and help improve adaptation to acute hypoxia and de-acclimatization.

**Clinical Trial Registration:** This study has been registered in the Chinese Clinical Trial Register (www.chictr.org.cn) as ChiCTR2200059900 and ChiCTR2200066328.

## Introduction

1

It is known that hypobaric hypoxia is the main characteristic of a high-altitude environment. Acute mountain sickness (AMS) is an environmental illness that can occur in people who arrive at high altitudes above about 2,500 m for the first time. The manifestations of AMS are a series of symptoms involving the brain, heart, gastrointestinal tract, and muscles (1). After returning to a low altitude, reoxygenation may also cause a series of symptoms, named high-altitude de-acclimatization symptoms (HADAS), which are adaptive reactions of the body when facing a normoxic environment (2). Both these symptoms stem from a maladaptation of the cardiovascular and respiratory systems when facing acute hypoxia and reoxygenation. Treatments targeting the cardiovascular and respiratory systems may alleviate these symptoms and help to restore cardiorespiratory fitness back to previous levels.

Reduced arterial oxygenation and increased pulmonary vascular resistance during acclimatization are the main causes of decreasing cardiorespiratory fitness at high altitude (3–6). Arterial oxygenation reduction is attributed to decreased partial pressure inspiratory oxygen and altered coupling of convectional and diffusional oxygen transport systems (7). Meanwhile, the elevated pulmonary vascular resistance is explained through hypoxia-induced pulmonary vasoconstriction and increased cardiac afterload in the right ventricle (8, 9). Although multiple reports have illustrated that the impairment of cardiorespiratory fitness is the main course of decreased physical performance capacity (10–12), there is far less information regarding the characteristics of cardiorespiratory fitness in the process of high-altitude acclimatization and de-acclimatization. Several prior attempts aimed to improve cardiorespiratory fitness after acute high-altitude exposure indicated that selective endothelin A receptor blockade, a PDE-5 inhibitor, and carbonic anhydrase inhibitor are beneficial in reducing cardiac afterload and restoring physical capacity (4, 13, 14). However, the severe side effects of sitaxsentan and acetazolamide limited their clinical applications, especially in elderly and severely ill patients (15, 16). Moreover, few studies have explored the potential medications for the prophylaxis and treatment of high-altitude de-acclimatization-associated symptoms and cardiorespiratory fitness impairment (17). Thus, exploring a new strategy to restore impaired cardiorespiratory fitness and exercise capacity during acclimatization and/or de-acclimatization is necessary.

Coenzyme Q10 (CoQ10) is a fat-soluble antioxidant occurring naturally in the inner membrane of the cell's mitochondria. It plays an essential role as a diffusible electron carrier in the electron transport chain (18, 19). CoQ10 has two forms: the oxidized form and the reduced, active form. This reduced form is widely used in the adjunctive treatment of cardiovascular diseases, nutritional health products, and food additives (20). Notably, CoQ10 plays a key role in myocardial hypoxia, significantly boosting heart health. In patients with myocardial ischemia and hypoxia, ubiquinol, the reduced-form supplement (19, 21, 22), increases aerobic metabolism efficiency and raises the anaerobic threshold. This signifies a lesser need to resort to anaerobic energy production at the same workload (19, 21, 22). Ubiquinol is necessary for the body to produce energy; however, its content in the organism decreases with age and may lead to diseases (23). The lack of ubiquinol causes less efficiency, quick fatigue, and weakened cellular protection ability against oxidative stress (19). These clinical trials implied that ubiquinol could reverse the loss of physical performance ability both at high altitudes and at return to sea level.

We designed this double-blinded, placebo-controlled clinical trial to investigate the hypothesis that ubiquinol supplementation could improve cardiorespiratory fitness, which may be impaired during high-altitude acclimatization and de-acclimatization. This novel Shigatse CARdiorespiratory Fitness (SCARF) study has the potential to identify whether ubiquinol supplementation may rescue the loss of exercise capacity and impaired cardiorespiratory fitness during acute hypoxia and the reoxygenation process. We believe this is the first study that prospectively and accurately evaluates cardiorespiratory fitness during high-altitude acclimatization and de-acclimatization. We also explore the effect of ubiquinol on blood metabolic substrate and automatic nervous function to illustrate the possible beneficial mechanisms further.

## Materials and methods

2.

### Setting

2.1.

This is a single-center, randomized, double-blind, placebo-control clinical trial conducted at Chongqing Xinqiao Hospital and Shigatse Branch Hospital [The Shigatse CARdiorespiratory Fitness (SCARF) Study] in 2022 and registered at www.chictr.org.cn (ChiCTR2200059900 and ChiCTR2200066328). The primary hypothesis of this study is that ubiquinol supplementation may improve cardiorespiratory fitness both at high-altitude acclimatization and de-acclimatization, while AMS and HADAS are secondary endpoints. The study complies with the SPIRIT 2013 recommendations (Standard Protocol Items: Recommendations for International Trials) (24) (Supplementary Material S1). Table 1 depicts the overall schedule and time commitment for trial participants.

**Table 1 T1:** Study schedule and time commitment.

Timepoint	Study period					
	Enrolment	Allocation	Post-allocation			Close-out
	−14 days	0	11 days	17 days	28 days	6 months
Enrolment						
Eligibility screen	X					
Informed consent	X					
Medical and travel history	X					
Vital signs	X					
Allocation/randomization		X				
Interventions						
Ubiquinol group						
Placebo group						
Assessments						
Baseline variables: age, sex, height, weight			X			
Outcome variables						
CPET			X	X	X	X
Blood routine examination			X	X	X	
Serum marker examination			X	X	X	
The Lake Louise 2018 score assessment				X		
High altitude de-acclimatization syndrome assessment					X	X

### Recruitment and study population

2.2.

Enrolment occurred in Chongqing (low altitude area, 300 m) from June 1st, 2022, and ended on June 15th, 2022. Demographic and medical data of all participants were recorded through interviews. A potential participant must meet all the inclusion criteria and do not meet any exclusion criteria. The inclusion and exclusion criteria are detailed in Table 2. According to previous studies, the risks associated with CoQ10 are minor, even at doses as high as 1,800 mg (25). Moreover, pharmacokinetic studies suggest that exogenous CoQ10 does not influence the biosynthesis of endogenous CoQ10 and is less likely to accumulate in plasma or tissues after the cessation of supplementation (26).

**Table 2 T2:** Inclusion and exclusion criteria.

Inclusion criteria	Age >18 years
	Chinese Han people
	Have no recent (previous 6 months) experience in resistance exercise (including additional cardiopulmonary exercise tests, long-distance running, riding, swimming and skiing and other endurance exercise)
	Are able to perform leg-based resistance exercise
	Are free from musculoskeletal injury (past 6 months)
	Lived at low altitudes (<500 m) for at least 10 years
	Had no recent exposure to high altitude (>2,500 m) (in the last 6 months)
	Willing and capable of providing written informed consent and complying with the study protocol
Exclusion criteria	Incapable of giving informed consent
	Respiratory and cardiovascular diseases
	Liver and kidney dysfunctions
	Malignant tumors
	Coagulation disorders
	A history of AMS
	History of angioedema
	A history of syncope (hypoglycemia excepted)
	Psychiatric disorders or neuroses
	Ubiquinol supplementation with any side-effect in the first 14 days before departure
	Pregnant or nursing women
	A recent history (previous 1-month period) of drug use with acetaminophen, aspirin, nonsteroidal anti-inflammatory drugs
	A recent history (previous 1-month period) of drug use of acetazolamide, diuretics, or other drugs for the prevention or treatment of AMS
	A recent history (previous 1-month period) use of consuming ergogenic aids (e.g., creatine monohydrate), protein-based supplements, or nutritional supplements that may alleviate muscle damage (e.g., antioxidants, polyphenols)
	Other diseases that prevent the patient from going to high altitudes
	Involuntary participant status

The study protocol complying with the Declaration of Helsinki was approved by the Medical Ethics Committee of Xinqiao Hospital of Army Medical University (No. 2022-060-01). All participants had to provide written informed consent after the study details, procedures, benefits, and risks were explained to them verbally and literally. Failure to do so resulted in their exclusion from this study.

### Sample size

2.3.

The G-power tool (version 3.1.9.2, Germany, 2017) was used to calculate the sample size by prior power analysis and to estimate all statistically significant results. The *α* error probability was set at 0.05, and the power (1 − *β*) was set at 0.9. With a correlation among repeated measures of 0.5, a sample size of 39 was determined to be necessary to assess the effects of ubiquinol. A sample size of 36 within two groups (ubiquinol group and placebo group) and within-between interactions were calculated with a nonsphericity correction (*ε*) of 1. Considering a 5% dropout rate, based on a sample size of 39, 41 participants would be required finally.

### Intervention

2.4.

#### Randomization, blinding, study treatment, and follow-up of participants

2.4.1.

Eligible subjects are randomized 1:1 into the ubiquinol group or placebo group by two physicians through a random code generator software (www.randomization.com) to receive either ubiquinol or placebo orally. These two physicians will solely operate randomization and drug distribution, and the randomization information will not be exposed to any participants or researchers, including laboratory staff, data gatherers, and statistical analysts throughout the study. Treatment allocation will be concealed in an opaque envelope opened on the day of treatment. Allocation will not be exposed until the end of the statistical data analysis or when any adverse event, such as severe diarrhea, occurs. A daily reminder email will be set up and sent to participants, and the rest of the medication will be sent back to us to assist in improving compliance. In addition, three serological tests of ubiquinol blood concentration can help monitor whether the participant is consistently taking the medication. The blinding will be maintained throughout the study. Clinical follow-up will be scheduled on days 11, 17, 28, and 6 months after the study began by performing cardiorespiratory tests or filling out self-administered questionnaires for symptoms. The primary outcome is cardiorespiratory fitness, while AMS and HADAS are the secondary endpoints. Safety endpoints include any reported adverse events (Table 3), exercise-limiting symptoms and pre-specified termination criteria (Table 4), and abnormal blood analysis results. The participants will have direct access to receive first aid from their treating team. Any adverse clinical event will be reported to the ethics committee.

**Table 3 T3:** Reported adverse events of ubiquinol (27).

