**1. Adverse drug reaction in the digestive system**
Upset stomach
Loss of appetite
Nausea
Diarrhea

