### The Lake Louise consensus scoring system and high-altitude de-acclimatization syndrome score

2.8.

The Lake Louise consensus scoring system 2018 version will be used to assess the presence of AMS at high altitudes according to the four main symptoms: headache, gastrointestinal symptoms, fatigue/weakness, and dizziness/vertigo. Scores of 0, 1, 2, and 3 correspond to none, mild, moderate, and severe degrees for each symptom, respectively. AMS is diagnosed as a total score of ≥3, combined with headache (1). We will collect this information every day through self-administered questionnaires at high altitudes.

The HADAS will be evaluated according to the scoring criteria for syndromes, which include complaining of dizziness, fatigue, weakness, headache, blurred vision, lethargy, insomnia, dreaminess, difficulty concentrating, memory loss, slow reaction, and physical signs, including chest tightness, cyanosis, palpitation, slow pulse, precordial pain, changes in blood pressure, decreased appetite, changes in body mass, abdominal distension, diarrhea, edema, constipation, cough, asthma, hair loss, sexual dysfunction, tooth loss, numbness of hands and feet, and skin hemorrhagic spots or ecchymosis (2). In addition, these symptoms do not improve under short-term rehabilitation after organic diseases of the heart, lungs, kidneys, and other organs are ruled out. Physicians who have been systematically trained will score the presence of three or more of the above symptoms or signs according to the following criteria: (1) have a slight reaction but not affect daily work for 0 points; (2) affect work but the symptoms improve soon after rest for score 1; (3) seriously affect daily work and symptoms improve significantly after drug treatment for score 2; (4) seriously affect daily work and symptoms do not improve significantly after drug treatment for score 3.

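### The unblinding rule (allocation exposed on any adverse event) contradicts the promise of blinding throughout, sets no threshold or recipient, and overlaps symptoms scored as AMS and HADAS

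*Protocol article*

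**What the plan says.** Section 2.4.1 of the protocol article makes three statements on blinding.

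- Only two physicians assign treatment and hand out the study product. For everyone else the rule is: "the randomization information will not be exposed to any participants or researchers, including laboratory staff, data gatherers, and statistical analysts throughout the study".
- The exception follows: "Allocation will not be exposed until the end of the statistical data analysis or when any adverse event, such as severe diarrhea, occurs".
- Three sentences after the exception: "The blinding will be maintained throughout the study".

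The exception names one example. It gives no grade of seriousness, no condition of clinical need, and no statement of who learns the allocation.

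The same section ties adverse events to a list: "Safety endpoints include any reported adverse events (Table 3), exercise-limiting symptoms and pre-specified termination criteria (Table 4), and abnormal blood analysis results". Table 3 grades none of its items by severity. Section 2.8 scores AMS daily by self-completed questionnaire on "headache, gastrointestinal symptoms, fatigue/weakness, and dizziness/vertigo", and diagnosis needs a total of at least 3 with headache. HADAS is scored by trained physicians from a long list of symptoms and signs.

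On adherence, section 2.4.1 adds that "three serological tests of ubiquinol blood concentration can help monitor whether the participant is consistently taking the medication".

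**The concern.** An emergency code-break provision is normal. The difficulty here is that the provision covers adverse events of any kind, sits beside two unqualified statements that nobody is unblinded, and uses symptoms that partly coincide with what the trial measures.

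If site staff followed the exception literally, a report of nausea or dizziness at altitude could expose that participant's allocation. Whoever then knew it might influence what follows. The exercise test runs until limiting symptoms, so peak oxygen uptake depends on effort. AMS is self-scored, and HADAS depends on a physician's judgement. Unblinding would also be related to symptoms rather than occurring at random, so it could differ between arms if ubiquinol affects those symptoms.

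**Working it through.** The plan states no figure on this point, so the check compares texts and makes one small count.

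**1. Do the statements conflict?** Two statements deny exposure to anyone during the study. One permits it on any adverse event before the analysis ends. Neither denial carries an exception, and the exception does not refer to the denials. The text must be reconciled.

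**2. Does the trigger overlap the outcomes?** Table 3 items set against section 2.8:

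| Table 3 item | Lake Louise item | HADAS item |
|---|---|---|
| Upset stomach, nausea | gastrointestinal | none |
| Loss of appetite | gastrointestinal | decreased appetite |
| Diarrhea | gastrointestinal (arguably) | diarrhea |
| Dizziness | dizziness/vertigo | dizziness |
| Insomnia | none | insomnia |
| Palpitation | none | palpitation |
| Hypertension, hypotension | none | blood pressure changes |
| Tachycardia, allergic reactions, anaphylactic shock | none | none |

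Two of the four Lake Louise items (gastrointestinal, dizziness) have Table 3 counterparts. Headache, which the diagnosis requires, and fatigue have none.

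**3. Could AMS usually be diagnosed without an overlapping symptom?** Each of the four items scores 0 to 3.

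- Patterns with headache of at least 1: 3 × 4 × 4 × 4 = 192.
- Of these, totals below 3: headache 1 with the other items summing to 0 or 1 gives 4 patterns; headache 2 with the others at 0 gives 1. So 192 − 5 = 187 patterns meet the AMS definition.
- Of the 187, patterns with no gastrointestinal or dizziness point: headache 1 with fatigue 2 or 3 (2), headache 2 with fatigue 1 to 3 (3), headache 3 with fatigue 0 to 3 (4), in all 9.
- So 187 − 9 = 178 patterns include at least one overlapping point.

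This counts possible patterns, unweighted. It is not a probability. It shows only that the partial overlap in step 2 is not negligible.

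**4. Is the order of events such that later data could be affected?** Section 2.6 places travel after 14 days of medication, follows AMS symptoms and ubiquinol reactions daily at altitude, and runs the exercise test on the third day there: 14 + 3 = day 17. Return comes after 7 days at altitude and the next tests 7 days later: 14 + 7 + 7 = day 28. A symptom on the first two days at altitude therefore precedes the day-17 test, the remaining AMS questionnaires, and the day-28 test and HADAS score.

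**5. How many participants?** The documents give no symptom rate. Purely as an assumption, if 10% to 60% of 41 reported a Table 3 symptom, the literal rule would reach 0.1 × 41 = 4.1 to 0.6 × 41 = 24.6 people, about 4 to 25. That range shows how open the rule is. It does not measure bias.

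**The case against.** The strongest defence is that this is an ordinary emergency code-break, badly phrased. The single example is a severe event. Section 2.6 lists AMS questionnaires and ubiquinol reactions as separate items of daily follow-up, and says the 14-day run-in is meant to help attribute altitude symptoms to hypoxia rather than to the supplement. Participants with adverse effects in the run-in do not travel, so a code-break at that stage leaves no altitude data to bias. Section 2.10 describes the exercise tests as run by a physician and a technician blinded to other procedures and details of the study. Table 3 is a list of reported reactions from a cited source and is not described as a trigger list. Table 4 holds exercise-test termination criteria and is a separate safety endpoint.

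Much of this stands, and it rules out stronger readings:

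- A reader might infer that participants with AMS will be unblinded. The text does not say who learns the allocation, and the stated intent is to keep altitude symptoms apart from ubiquinol reactions.
- A reader might infer that AMS symptoms as a whole are on the adverse-event list. Only two of the four items are.
- A reader might infer that this strikes the most important outcome directly. AMS and HADAS are secondary; the primary outcome is cardiorespiratory fitness, which could be affected only through later tests.
- A reader might infer that ubiquinol levels reveal the arm to laboratory staff and analysts. A level that shows intake could do so, but the article does not say when the assay is run or who sees the result, and a full protocol may settle that.

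The defence does not remove the contradiction. The stated intent is not a classification rule: nothing says whether nausea or dizziness at altitude is recorded as AMS, as an adverse event, or as both. The run-in does not cover events that first appear at altitude or after return. Blinded test staff do not protect against a change in a participant's own effort or self-scoring if that participant learns the allocation.

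**Conclusion.** The point holds as a contradiction in the text and an unblinding trigger fixed too broadly. Section 2.4.1 both permits and denies exposure of allocation during the study, without threshold or recipient. The overlap with two of four Lake Louise items and several HADAS items means that a literal reading could tie unblinding to the secondary outcomes and affect later effort-dependent exercise tests. That consequence is a risk under the wording as it stands, not a documented event.

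No magnitude of bias can be derived. It would need the symptom rate, the share of such symptoms handled as adverse events, who was told, and the effect of knowing on effort or scoring, and the documents give none of these. A figure obtained by multiplying an assumed symptom rate by an assumed shift in effort would reflect only those assumptions. The assay route is a plausible risk that justifies a precaution and no more.

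**What to change.** - **Reconcile the three sentences.** Allow a code-break only when the allocation is needed for a participant's care, and disclose it only to those who need it. Outcome assessors, exercise-test staff and analysts stay blind. Which events meet that need is for the investigators to define.
- **Classify shared symptoms.** State that symptoms scored as AMS or HADAS do not by themselves trigger exposure.
- **Log and report.** Record every code-break by arm and date, including any that have already occurred, and who was told.
- **Add a sensitivity analysis** that excludes outcome data collected after a code-break. It should support the main analysis and not replace it, because the excluded data would be selected by symptoms.
- **As a precaution,** withhold ubiquinol concentrations from blinded staff until the outcome data are locked.

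The cost is wording, a log, one extra analysis and the routing of one assay. The small downside is that blinded staff lose real-time adherence feedback from blood levels; returned medication still provides some. Enrolment closed in June 2022 and section 2.6 names only the six-month visit as still to come, so rewording would probably not protect the earlier visits. The main gain now is to protect the remaining assessments and the analysis, and to report openly any code-breaks that took place.
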